## Abstract

**Background:**

Regular physical activity (PA) is recommended to optimize weight and health outcomes in patients who have undergone metabolic and bariatric surgery (MBS). However, >70% of patients have low PA levels before MBS that persist after MBS. Although behavioral interventions delivered face-to-face have shown promise for increasing PA among patients who have undergone MBS, many may experience barriers, preventing enrollment into and adherence to such interventions. Delivering PA behavior change interventions via telehealth to patients who have undergone MBS may be an effective strategy to increase accessibility and reach, as well as adherence.

**Objective:**

This paper reports the protocol for a study that aims to assess the feasibility and acceptability of the protocol or methods and the Telehealth Bariatric Behavioral Intervention (TELE-BariACTIV). The intervention is designed to increase moderate-to-vigorous intensity PA (MVPA) in patients awaiting bariatric surgery and is guided by a multitheory approach and a patient perspective. Another objective is to estimate the effect of the TELE-BariACTIV intervention on presurgical MVPA to determine the appropriate sample size for a multicenter trial.

**Methods:**

This study is a multicenter trial using a repeated (ABAB’A) single-case experimental design. The A phases are observational phases without intervention (A1=pre-MBS phase; A2=length personalized according to the MBS date; A3=7 months post-MBS phase). The B phases are interventional phases with PA counseling (B1=6 weekly pre-MBS sessions; B2=3 monthly sessions starting 3 months after MBS). The target sample size is set to 12. Participants are inactive adults awaiting sleeve gastrectomy who have access to a computer with internet and an interface with a camera. The participants are randomly allocated to a 1- or 2-week baseline period (A1). Protocol and intervention feasibility and acceptability (primary outcomes) will be assessed by recording missing data, refusal, recruitment, retention, attendance, and attrition rates, as well as via web-based acceptability questionnaires and semistructured interviews. Data collected via accelerometry (7-14 days) on 8 occasions and via questionnaires on 10 occasions will be analyzed to estimate the effect of the intervention on MVPA. Generalization measures assessing the quality of life, anxiety and depressive symptoms, and theory-based constructs (ie, motivational regulations for PA, self-efficacy to overcome barriers to PA, basic psychological needs satisfaction and frustration, PA enjoyment, and social support for PA; secondary outcomes for a future large-scale trial) will be completed via web-based questionnaires on 6-10 occasions. The institutional review board provided ethics approval for the study in June 2021.

**Results:**

Recruitment began in September 2021, and all the participants were enrolled (n=12). Data collection is expected to end in fall 2023, depending on the MBS date of the recruited participants.

**Conclusions:**

The TELE-BariACTIV intervention has the potential for implementation across multiple settings owing to its collaborative construction that can be offered remotely.

**International Registered Report Identifier (IRRID):**

DERR1-10.2196/39633

## Introduction

### Background

Severe obesity (class II and III; BMI ≥35 kg/m^2^) affects approximately 9.5% of Canadians [1]. Metabolic and bariatric surgery (MBS) is generally effective in inducing significant and lasting weight loss [2] while reducing the costs related to severe obesity and associated complications [3,4]. MBS offers significant health benefits and improves the quality of life [4,5]. The number of procedures performed worldwide has increased during the last decade in particular, reaching almost 700,000 surgeries performed in 2018 [6]. However, approximately half of the patients who have undergone MBS regain at least 10% and 20% of their maximum weight loss 1 year and 5 years after reaching their nadir weight, respectively [7].

In the context of MBS, physical activity (PA) is recommended given its multiple benefits [8,9]. Studies have shown that pre- and post-MBS PA can improve physical fitness, cardiometabolic health, quality of life, and depressive symptoms [10-17]. However, 70% to 95% of adults are inactive before MBS and remain so after MBS [18,19]. Thus, there is a need to develop interventions with the aim of increasing pre- and post-MBS PA. Introducing PA behavior change interventions before MBS with additional support offered after MBS seems to be an ideal approach to optimize MBS benefits and provide transitional support toward post-MBS lifestyle [20]. The most compelling evidence to support this assertion comes from studies that have shown that PA interventions delivered before MBS can increase PA until 1 year after MBS [21,22]. Furthermore, pre-MBS PA can improve physical fitness, which may help reduce perioperative complications and length of hospital stay [23]. Finally, participants’ motivation and readiness for PA increased close to their surgical date [24].

Supervised exercise within the context of clinical- and research-based interventions, although effective in conferring health benefits, does not increase long-term PA in adults undergoing MBS [17,25,26], likely because this type of intervention almost never includes behavioral change methods (ie, no target of PA determinants such as self-determination and self-efficacy that may help with maintenance of PA behavior). Interventions that apply methods specifically targeting PA determinants are needed to equip adults with the knowledge, skills, and confidence to engage in regular PA on their own, as resources are not infinite. Therefore, PA behavior change interventions should be considered, which can be effective in increasing PA in adults with obesity [27]. In adults undergoing MBS, Bond et al [22,28,29] have shown that BariActiv, a 6-week intervention delivered before MBS, which included weekly one-on-one meetings and focused on behavior change techniques (BCTs), increased moderate-to-vigorous intensity PA (MVPA) and step counts after the intervention, and these changes were sustained 6 months after MBS. Thus, PA behavior change interventions seem promising to increase MVPA in the midterm and, in turn, limit weight regain to maintain health improvements. However, additional studies investigating the effects of behavior change interventions on MVPA are required owing to the heterogeneity and small number of studies available and the divergent results across studies with adults undergoing MBS [30].

### Successful Behavior Change Interventions Targeting PA

#### Overview

Successful behavior change interventions are based on evidence and a good understanding of the targeted behavior and its correlates, context, and population [31,32]. Such interventions also require input from stakeholders, especially those who will receive it, which can be obtained via various methods. For example, to inform theory- and evidence-based decisions about the design and delivery of PA behavior change interventions, a web-based survey and focus groups were conducted with adults undergoing MBS living in Quebec, Canada [33]. The results highlight 4 fundamental points to consider when developing a behavior change intervention to promote PA among adults undergoing MBS.

#### Needs Assessment and Patient Perspectives

First, the main PA motives before and after MBS include weight control, social support, pleasure, well-being, and physical fitness [34-40]. Therefore, PA interventions should identify strategies addressing these motives to meet patients’ expectations and keep track of these for efficacy evaluations. Second, motivating adults to engage in PA, either before or after MBS, is challenging because of several barriers [41-44], including physical and psychological issues, such as pain, fatigue, weight, lack of motivation, and body dissatisfaction [34-40]. Other important PA barriers reported include perceived lack of time and resources, bad weather, and lack of social support [34-40], which can persist after MBS despite weight loss and health improvement [45]. In addition, new PA barriers may emerge after MBS caused by excess skin [46,47]. Accordingly, adults are likely to need support to overcome barriers to PA both before and after MBS. Ensuring that a well-trained PA counselor who can help intended users elucidate barriers and identify means to create an environment that makes PA easier and reduces barriers to action is important. Third, adults reported a preference for PA interventions starting 3 to 6 months before MBS and being offered continued support until 1 year after MBS [33], suggesting that initiating a PA behavior change intervention before MBS, with additional post-MBS follow-ups, may be most acceptable. Fourth, interventions offering face-to-face meetings with health professionals are preferable [33]. Accordingly, integration of supervision via regular meetings should thus be considered as a key element to enhance participants’ adherence to the intervention and, in turn, their PA [48,49].

#### Multitheory Approach

Beyond the aforementioned considerations, it is necessary to draw on behavior change theories to target specific factors that influence PA behavior when developing PA behavior change interventions. Existing theories such as self-determination theory (SDT) [50] and social cognitive theory (SCT) [51] are 2 theories previously used in PA behavior change interventions [52], as they are especially relevant in identifying determinants of PA. SDT suggests that an individual’s motivation to engage in a behavior, such as PA, is based on the satisfaction of their basic psychological needs of competence, autonomy, and relatedness [50]. From an SDT perspective, interventions can enhance needs satisfaction by providing autonomy support (ie, providing PA choices and minimizing perceived pressure) and structure (ie, communicating clear expectations, providing access to personalized information, and providing feedback) and by building strong interpersonal relationships with participants [50]. In turn, when an individual’s needs are satisfied and their motivation to engage in a behavior is internalized and for self-determined reasons, because PA is enjoyable, pleasurable, of interest, and aligned with their values, their behavior is more likely to become habitual and maintained over time. Both quantitative and qualitative studies support these tenets [29,53,54]. SCT suggests that self-efficacy is a key determinant of PA [51]. From an SCT perspective, interventions fostering an individual’s perceived self-efficacy via positive reinforcement can help promote PA uptake and adherence [55].

Using SDT and SCT when planning PA behavior change interventions, several studies have shown that targeting their underlying theoretical constructs (eg, perceptions of competence, autonomy and relatedness, motivational regulations, and self-efficacy) and introducing evidence-based motivational and behavior change techniques (MBCTs) can have a positive effect on PA outcomes [27,44,56]. MBCTs include shaping knowledge (ie, providing instruction on how to perform the behavior and how to monitor the behavior and affect), comparison of outcomes (ie, discussing pros and cons), natural consequences (ie, providing information about the health benefits of PA and monitoring of benefits or outcomes), goal setting (ie, setting goals, problem solving, action planning, discrepancy between current behavior and goal, review outcome goal or goals, behavioral contract, and commitment), fostering self-beliefs via verbal persuasion about the capability to overcome barriers, focus on past success, and self-talk, feedback, and monitoring (ie, providing feedback on behavior, self-monitoring of outcome or outcomes of behavior, and self-monitoring of behavior), associations (ie, picking prompts and cues), and rewards and threats (ie, building self-rewards) [27,44,56]. Collectively, studies have shown that a variety of SDT- and SCT-based interventions, including MBCTs, are promising for increasing PA in people with overweight or obesity [56,57]. However, no single theory has shown superiority in its ability to increase PA, and there is an increasing trend to include multiple MBCTs that map onto multiple theories to ensure that several key factors influencing PA are targeted [52,56]. As such, rather than choosing one theory, PA behavior change interventions including MBCTs related to SDT and SCT constructs should be considered, as they may increase the likelihood that patients awaiting MBS will initiate and maintain their PA.

### Approaches to Delivering Interventions

PA behavior change interventions for adults with obesity include center-, community-, and home-based programs. However, alternative delivery formats, including email, phone, or videoconferencing counseling, have also been shown to be effective [58]. Videoconferencing counseling, otherwise referred to as telehealth interventions, have been introduced to address key issues and patients’ preferences (eg, lack of time and resources, supervision, face-to-face, accessibility, and simplicity) while considering current contextual challenges (eg, limited financial and human resources, travel to and from MBS or research centers, pandemic lockdown, and environmental concerns) and maintaining opportunities for meetings with health professionals as per patient preferences. Therefore, it is important to develop and implement behavior change interventions using telehealth.

Telehealth refers to the use of the internet and connected technologies to provide care [59], and adherence rates as acceptability of such interventions are high (≥75%) [60-64]. The feasibility of telehealth interventions is very promising given the ubiquitous access to the internet and technologies in Canada, with 94% of residents having access to the internet and 88% owning a smartphone [65]. Moreover, telehealth is cost-effective and has already been shown to improve health outcomes [60,62,66] and PA among adults with or without obesity [67,68]. Although many studies are available on telehealth interventions with patients who had undergone MBS [69-74], to our knowledge, only 3 of them included a PA behavior change intervention: 1 feasibility study before MBS (before-after study design) [72]; 1 feasibility study after MBS (before-after study design) [73]; and 1 ongoing randomized controlled study after MBS [74]. However, PA was generally self-reported and was only measured in the short term, introducing measurement bias and preventing the assessment of PA maintenance [71]. Robust and innovative study designs, such as a single-case experimental design with long-term objective PA measures, should be used in future studies to assess the effects of telehealth PA behavior change interventions in the short and long term. Therefore, Bari-Activ, having already shown its efficacy [22,28,29], was revised to reinforce theory-based content, reflect intended users’ perspectives and the context in which the intervention will be conducted, and provide a means to increase reach (via telehealth). It will be tested within a single-case experimental design to ensure that it is feasible and applicable to intended users and implementers and generate data to inform a large-scale trial to test whether it is effective.

### Objectives

This manuscript reports the protocol used in this study. The first objective is to assess the feasibility and acceptability of the protocol or methods and the Telehealth Bariatric Behavioral Intervention (TELE-BariACTIV), an intervention designed to increase MVPA that is guided by two perspectives: (1) a multitheory approach, thus targeting SDT and SCT constructs and integrating related MBCTs, and (2) a patient perspective. The second objective is to generate an estimate of the effect of the TELE-BariACTIV intervention on presurgical MVPA (the primary outcome for a future large-scale trial) to determine the appropriate sample size for a multicenter large-scale trial.

## Methods

### Study Design and Procedures

The study uses a phased approach to behavior change intervention development supported by the Obesity Related Behavioral Intervention Trials model [31].

The study results will be reported according to the recommendations for single-case protocols in behavioral interventions [75]. Owing to the objectives of the study (feasibility, acceptability, and effect size exploration) and recommendations [31,76], this study is a multicenter study with a single-case experimental design with multiple base levels (ABAB’A). It is an open-label trial in which research staff, researchers, and participants are not blinded to the study objectives, intervention, and allocation, given the nature of the intervention and measures.

Approximately 2 weeks before the baseline assessment, the study will be explained by phone to potential participants and the selection criteria, checked. Eligible and interested participants will be sent an accelerometer and a A370 Polar (Polar Electro) watch with cables to recharge and information sheet by mail with a prepaid return envelope. Participants will be instructed to initiate the baseline assessment on the web (Limesurvey) once they receive their packages, including an informed consent form. Then, participants will be randomly allocated to a 1- or 2-week baseline A1 phase using a list of random numbers generated electronically by a person outside the project, and they will start the 5 phases of the study (A1-B1-A2-B2-A3; Figure 1). The A phases are observational phases without intervention, and the B phases are intervention phases with PA counseling delivered via Zoom technology platform. Participants had different dates of starting the study owing to the variability in their MBS dates. Phase A2 may also vary in length because the exact MBS date is usually not known when participants are to start the study.

To meet the design standards that recommend at least 3 measurements per phase [75,77], MVPA is assessed continuously over 7 to 14 days during each phase. The storage limit of the accelerometer is 180 days, which ensures the feasibility of the measurement. Therefore, participants have to download the free Actisync application on a computer, connect the device with a cable, and then upload their anonymized accelerometry data using the Actigraph Centerpoint minimum every 180 days. Quality of life, anxiety and depressive symptoms, motivational regulations, basic psychological needs satisfaction and frustration, self-efficacy to overcome barriers to PA, PA enjoyment, and social support for exercise are assessed using a series of validated questionnaires 6 to 10 times via Limesurvey (Table 1). In addition, participants are asked to respond to questions regarding the acceptability of the protocol and intervention in web-based questionnaires before and after the intervention (phase B1), as well as during a web-based semistructured individual interview 1 to 4 weeks after phase B1. Medical records will be consulted at the end of the study with the participants’ authorization to validate the MBS date, medical conditions, and weight loss.

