#### Secondary Outcomes

##### MVPA (Primary Outcome for the Future Large-scale Trial)

Daily MVPA is directly assessed using a triaxial accelerometer worn at the hip on the right side (Actigraph wGT3X-BT) during phase A1 and then for 7 days during the other assessment time points (Figure 1). Participants are instructed to wear the accelerometer continuously, except during water-based activities, and to maintain a log of wear times with waking and bed times. Accelerometer data will be extracted and downloaded (10-second epochs) using Actilife version 6.13.4 and will be cleaned in accordance with the logbooks provided by the participants. Only data from participants who wear the accelerometer for ≥3 days (including at least 1 weekday and 1 weekend day) and ≥10 hours/day will be analyzed [18,81]. The nonwear time is defined as a period of ≥120 minutes of consecutive zeros [82]. Accelerometer data will be used to quantify the time spent in MVPA (min/day). As PA intensity classifications have not yet been established for adults undergoing MBS, existing threshold values for the general population will be used for analyses (moderate-intensity PA=1952-5724 and vigorous-intensity PA 5724 counts/min) [83].

Data gathered immediately after phase B1 will be used to estimate effect sizes to determine sample size calculation for a future large-scale trial. Achieving PA recommendations of ≥150 min/week of MVPA will be judged as clinically significant [84,85].

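### The reason given for having no blinding does not cover accelerometer processing, and logbook cleaning is the one step where knowing the phase could affect daily MVPA

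*Protocol article*

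**What the plan says.** Study Design and Procedures describes an open-label trial in which staff, researchers and participants alike are "not blinded to the study objectives, intervention, and allocation, given the nature of the intervention and measures". One reason thus serves for all of them. The same section has participants "upload their anonymized accelerometry data using the Actigraph Centerpoint", and says the random list for the 1- or 2-week baseline was "generated electronically by a person outside the project".

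The section on MVPA as the primary outcome for the future trial fixes most of the processing by number. Data count from participants who "wear the accelerometer for ≥3 days (including at least 1 weekday and 1 weekend day) and ≥10 hours/day". Nonwear is a "period of ≥120 minutes of consecutive zeros". Epoch length, software version and intensity cut points are also set. Participants keep a log of wear, waking and bed times, and the accelerometer data "will be cleaned in accordance with the logbooks provided by the participants".

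Statistical Analyses compares daily MVPA in A1 with B1 for each participant and pools the individual effects to obtain the sample size for the large-scale trial. Objectives lists that estimate as the second objective.

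**The concern.** A single reason is used to leave every step unblinded. For live counseling, interviews and self-report it is sound. For a device file it is not, because nothing in how the file is recorded requires the person who later cleans it to see the phase.

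This matters because each participant serves as their own control. Phase is the contrast, so knowing the phase during data processing is like knowing the arm in a parallel-group trial. When a log and a device record disagree, settling the conflict can decide whether certain hours count as wear and so whether a day reaches 10 hours. If such decisions leaned one way in A1 and the other way around B1, they would enter the MVPA effect and pass into the planning of the next trial. The Introduction faults earlier work for measurement bias from self-reported activity, and unmasked log reconciliation gives up part of the advantage of an objective measure.

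**Working it through.** There is no stated figure to reproduce. The sample size of 12 is justified by the design, and the article gives no day-to-day SD of MVPA and no frequency of contestable days. The check has two parts.

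**1. Where judgment can enter**

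| Step | Rule in the article | Room for judgment |
|---|---|---|
| Nonwear | ≥120 min of consecutive zeros | none |
| Valid day | ≥10 hours/day | none once wear time is settled |
| Valid record | ≥3 days, with 1 weekday and 1 weekend day | none |
| Intensity | fixed counts/min cut points | none |
| Cleaning against logs | no conflict rule stated | yes |

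Only the last row leaves room for judgment.

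**2. What one decision could do**

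Inputs from the article: each window is 7 days (A1 is 7 or 14). Table 1 gives B1 a mid-phase and an after-phase window, so the A1-B1 comparison could use 7 or 14 B1 days. Assumptions: days are independent, there is no true change, and the contested day is also the lowest-MVPA day of its window.

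For n days with the lowest removed, the mean rises on average by

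shift = E(depth of the minimum below the mean, in day-SD) / (n − 1)

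- 7 normal days: 1.352 / 6 = 0.225 day-SD (simulation: 0.225 to 0.227)
- 7 log-normal days (sigma 0.8): 0.127 day-SD by simulation
- 14 normal days: 0.131 day-SD by simulation
- 14 log-normal days (sigma 0.8): 0.065 day-SD by simulation

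So the range is about 0.13 to 0.23 day-SD for one 7-day window, and about 0.06 to 0.13 if both B1 windows are used.

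Converting to minutes requires an SD that the article does not give. For an assumed day SD of 10 to 20 min, the 7-day case runs from 0.127 × 10 = 1.3 to 0.225 × 20 = 4.5 min/day. Over a week that is 1.27 × 7 = 9 to 4.5 × 7 = 32 min. These figures show what one favorable decision does in one participant's window. They are not an expected bias.

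If the cleaning cannot see the phase, exclusions cannot depend on it, and the expected distortion from this source is zero.

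**The case against.** The strongest reply is that the article never says who cleans the files or which labels that person sees. The open-label sentence is general, uploads are anonymized, and a journal article may leave processing detail to a fuller document. Day validity is numeric, and participants are told to wear the device continuously except in water, so days near 10 hours may be rare. The illustration also needs the contested day to be the lowest one. Masking would leave untouched participants' own reactivity to being measured, which may be the larger problem. The primary outcomes are feasibility and acceptability.

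Most of this stands, and it rules out three readings that a reader might infer:

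- **Files are cleaned by staff who know the phase.** This follows only from the blanket statement about staff and researchers. The article does not say it of file cleaning.
- **Days are excluded at discretion.** The wear rules are fixed, and discretion is confined to reconciling log and device.
- **The A1-B1 effect is inflated and the next trial will be underpowered.** Neither direction nor frequency can be derived from the document. A lost-power figure would also require treating within-person day-SD as a between-person standardized effect.

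The reply does not remove the core point, which concerns a reason the article states, not a detail it omits. That reason is given for all measures and is wrong for device files. Anonymizing a file by identity does not hide its phase or date.

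**Conclusion.** The point holds in a limited form. The nature of the measures does not justify unblinded processing of accelerometer files, and logbook cleaning is the one step where judgment could depend on knowing the phase. A resulting bias in the MVPA effect used to size the future trial is possible, with unknown direction and size. The upper-bound illustration is about 0.13 to 0.23 day-SD for one dropped day in one 7-day window, smaller with 14 B1 days. It rests on independent days, the assumed normal or log-normal shape, and the worst-placed day being the one contested. For a 12-participant feasibility study this is a worthwhile low-cost improvement and no more.

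**What to change.** 1. Cut the assessment windows by script. One upload may span several phases, since the device stores up to 180 days.
2. Replace phase and dates on each file and its log page with a random code and day of week. Code a 14-day A1 as two 7-day segments so that length does not reveal the phase. The person outside the project who made the random list, or a script, can hold the key.
3. Reconcile logs and apply the nonwear and 10-hour rules on the coded files, or do this with a fixed script that includes a rule for log-device conflicts. Lock the day-level data.
4. Restore phase labels, then apply the ≥3-day, weekday-plus-weekend rule to the whole phase window. Applying it to each half of a 14-day A1 would change the criterion.
5. In Study Design and Procedures, limit the no-blinding reason to counseling, interviews and participant-reported measures, and state that accelerometer processing is masked to phase or scripted.

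The cost is a short recoding script and a lock step, with no extra assessor or visit. There is slightly more data handling. Enrollment was complete by July 2022 and the pre-surgery analysis was planned for fall 2022, so any files already cleaned would need re-running. Participant reactivity is not removed.
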